## Methods/design

### Aim, design and setting of the study

This is a prospective longitudinal cohort study that will include eighty non-selected consecutive subjects ranging from 70 to 85 years old with severe AS with an indication for AVR and an intermediate or high surgical risk. The participants will be evaluated by the Heart Team of a Comprehensive Center (Germans Trias i Pujol Hospital) that will assign them to SAVR, TAVI, or conservative treatment. Despite the limitation of this is not a randomized study; only those subjects who are suitable for both interventions will be included (and in many cases, the decision to undertake one treatment or another will made on the basis of availability for one or another technique). Subjects will be evaluated in three time periods: at baseline, within 1 month prior to intervention, 1 month after the intervention (early follow-up), and 1 year after the intervention (late follow-up). Throughout these periods, all study subjects will concomitantly undergo an extensive clinical examination, including neurological examination, neuropsychological evaluation, and advanced neuroimaging protocol to determine clinical and silent stroke events and cognitive status. In addition, we will study the correlation between neuropsychological and neuroimaging findings.

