### Statistical considerations

The sample size calculation will be based on the main variable of the study, Impairment Index or Global Cognitive Impairment Index, which will be handled as a standardized normal distribution (mean=0 and SD=1). The way to transform the values of every subject to a standardized value is using the formula (value-mean)/SD. With this approach, we can estimate the difference between groups as a difference in the standardized normal distribution (z score), avoiding to approximate or guess values of SD that we do not previously know.

Establishing an alpha error of 5% and a beta error of 20% (80% statistical power), for a two-sided analysis and an effect size to observe defined as a minimal difference in z score of 0.67. Applying these criteria, an estimate of 36 patients per group is obtained. Assuming a loss of follow-up of 10%, we aimed to recruit 40 patients per group. The statistical package used for sample calculations was Stata 14.2 (StataCorp LLC, College Station, Texas, USA).

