A descriptive analysis of the sample will be carried out based on the characteristics of each variable. Continuous variables will be expressed as mean and 95% confidence interval, or median and interquartile range for each of the study groups, choosing the most appropriate description according to the result of the Shapiro-Wilk normality test. Categorical variables will be expressed with their absolute frequency (count) and relative frequency (as a percentage).Data cleansing and exploration of missing values will be carried out. Missing data greater than 10% will be considered excessive, deciding whether to maintain the variable in the study according to its importance in the literature and in the study design. For missing data recognized as excessive in clinically important variables, the dataset will be completed using multiple imputation techniques. Student t-test will be preferred for the crude comparative analysis between groups as a bilateral parametric test that will allow us to find differences in both directions of the hypothesis, given the heterogeneity of the existing literature. Equality of variances will be tested using the Levene test to adjust the standard error in the comparison. Sample size should ensure the conditions of application of parametric tests.The statistical adjustment of confounding factors and interaction of predictors will be carried outby building an explanatory model using multivariate linear regression, thus obtaining the coefficient corresponding to the main variable adjusted by the rest of potentially confounding or effect-modifying variables. First, a univariate screening of variables will be carried out, introducing in the model those which present confounding criteria based on the Pearson correlation test. Subsequently, first-order interactions will be explored based on statistical significance tests. The adjustment of confounding factors will be carried out based on relevant modification criteria (larger than 10%) of the model coefficients, according to the methodology described by Kleinbaum et al [58], and applying the principle of parsimony. The search for independent predictors of neuropsychological dysfunction will be carried out using a predictive approach of hierarchical logistic regression with a stepwise backward methodology.An analysis of residuals and extreme values will be carried out to verify the robustness of the built model. For the rest of the secondary hypotheses, mean comparison techniques (Student's t-test with adapted standard error) and proportions (chi-square) will be used.

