Along with the neuropsychological study, which is the goal standard in the diagnosis of cognitive impairment, including VCI, neuroimaging with MRI is key to objectifying the lesions that are probably the origin of alterations in cognitive domains. In addition, functional MRI will allow us to study pathways and brain functions, as well as establish the correlation between the findings with the results of the neuropsychological study. The potential usefulness that can be obtained with the data from our study could mean using neuroimaging as an alternative to the neuropsychological study in those patients with cognitive alterations or with language alterations, such as aphasia, or of the senses such as hearing or sight, that do not allow the administration of all or some neuropsychological tests.

Strengths of this study are: 1). Although patients will not be randomized between SAVR and TAVI, they are eligible for inclusion in the study only if they are suitable for both techniques; therefore the groups will be comparable; 2). To the best of our knowledge, this is the first study that simultaneously uses an extensive neuropsychological study, with a battery designed to evaluate all domains likely to be affected in the VCI, and an advanced MRI study, with sequences to assess structural damage as well as a functional MRI to compare SAVR and TAVI in patients with severe aortic stenosis; 3). In addition, these studies will be carried out pre-treatment, in the early phase and in the late phase; 4). and will have the participation of a vascular neurologist who will evaluate the patients and the clinical events that they may present following the recommendations of the NeuroARC.

We hope that all the information obtained from ARTiCO study will contribute to a better understanding of the changes that occur in neurocognition after the two distinct types of treatment available for severe AS and therefore, that it helps Heart Teams in decision-making.

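### The primary between-group model is not designated, and its confounders are chosen by an under-defined, data-driven screen that does not guarantee adjustment for baseline GCII

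*Protocol article*

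**What the plan says.** - Design: under Aim, design and setting of the study, the Heart Team assigns treatment. The article concedes the point ("Despite the limitation of this is not a randomized study") and says that availability of a technique decides in many cases.
- Crude analysis: "Student t-test will be preferred for the crude comparative analysis between groups".
- Adjusted analysis: a linear regression that yields a treatment coefficient adjusted for possible confounders and effect modifiers. Covariates are picked by "introducing in the model those which present confounding criteria based on the Pearson correlation test". Then "first-order interactions will be explored based on statistical significance tests". Confounders stay if they move the model coefficients by more than 10%, subject to parsimony.
- No covariate is named as mandatory. The section does not say which of the two analyses is primary, or whether the dependent variable is follow-up GCII or its change.
- The Discussion lists as a strength that patients must be suitable for both techniques, and concludes "therefore the groups will be comparable".
- Age and education enter through the norms used to form the z scores (Neuropsychological assessment).

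**The concern.** In a non-randomised comparison the adjustment carries the causal claim, so the rule that decides what is adjusted for should be fixed and unambiguous. Here the rule is stated but can be read in ways that lead to materially different models.

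Baseline GCII is the covariate most at stake. The battery is given to everyone before treatment. The article itself treats baseline cognition as prognostic: the Background stresses pre-intervention testing, and the Discussion cites a meta-analysis in which pre-existing impairment predicted poorer outcomes after TAVI. Yet baseline GCII enters the model only if it survives the selection.

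Suitability for both techniques narrows the population but does not balance the arms within it. Where availability did not decide, something else did, and that reason may be related to cognition, vascular burden or general risk.

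**Working it through.** **1. The plan's own figure.** Inputs from Statistical considerations: "Establishing an alpha error of 5% and a beta error of 20% (80% statistical power), for a two-sided analysis"; "an effect size to observe defined as a minimal difference in z score of 0.67"; GCII "which will be handled as a standardized normal distribution (mean=0 and SD=1").

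n per group = 2 × (1.960 + 0.842)² × 1² / 0.67² = 34.97, so 35 by the normal approximation. The t-distribution version gives 35.96, so 36. With 10% loss, 36 / 0.9 = 40. The stated 36 and 40 reproduce. They correspond to an unadjusted two-sample comparison with no baseline term.

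**2. Assumptions (none is in the article).** Baseline to follow-up correlation ρ of 0.5 to 0.8; baseline GCII imbalance d of 0.3 or 0.5 SD between groups; Pearson threshold p < 0.05. The simulations used 36 per group and 6,000 runs.

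**3. What a baseline imbalance does if there is no true effect.**
- Crude difference in follow-up GCII: bias = ρ × d. At d = 0.3 this is 0.15 (ρ 0.5) to 0.24 (ρ 0.8).
- Difference in change scores: bias = −(1 − ρ) × d. At d = 0.3 this is −0.15 (ρ 0.5) to −0.06 (ρ 0.8), which is regression to the mean.
- Regression with baseline GCII always included: bias about 0.

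**4. What the planned screen does, by reading.**
- *Association with both treatment and outcome required.* The treatment test is the bottleneck. At d = 0.3 its expected statistic is 0.3 / √(2/36) = 1.27 against a critical value of 1.99, so baseline passes with probability of about Φ(−0.72) = 0.24. At d = 0.5 it is 2.12, giving Φ(0.13) = 0.55. The simulation agrees (about 24% and 55%).
- *Association with outcome only.* Baseline GCII passes in at least 99.6% of runs.

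| No true effect, d = 0.3 | ρ 0.5 | ρ 0.7 | ρ 0.8 |
|---|---|---|---|
| Bias, crude t-test | 0.148 | 0.212 | 0.241 |
| Bias, screen on both | 0.077 | 0.110 | 0.127 |
| Bias, outcome-only screen | about 0 | 0.000 | 0.001 |
| Bias, baseline always in | about 0 | 0.000 | 0.001 |
| Rejection rate, crude t-test | 9.4% | 14.5% | 17.4% |
| Rejection rate, screen on both | 5.7% | 5.9% | 5.4% |
| Rejection rate, baseline always in | 5.5% | 5.1% | 4.8% |

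At d = 0.5 the screen on both leaves bias of 0.068, 0.090 and 0.103.

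**5. The 10% rule.** Added to the outcome-only screen, it keeps baseline GCII in 68% to 99% of runs, with bias still about 0. The lowest figure (68%) arises with a true effect of 0.67 and no imbalance, where baseline serves precision only.

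**6. Power and precision.**
- At ρ = 0.7, a true effect of 0.67 and a 0.3 SD imbalance against the better arm, power is 68.8% with the screen on both and 96.9% with baseline always in.
- With no imbalance, the 95% CI half-width is 1.96 × √(2/36) × √(1 − ρ²): 0.46 without baseline, 0.40 at ρ 0.5, 0.33 at ρ 0.7 and 0.28 at ρ 0.8.
- Compared with change scores, variance falls from 2(1 − ρ) to 1 − ρ². At ρ 0.7 that is 0.60 to 0.51, a 15% reduction. Compared with raw follow-up scores it is 1 to 0.51, or 49%.

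**The case against.** A reader might infer that the crude t-test is the primary contrast, so that the estimate simply stays confounded and imprecise. The article does not support this. It labels the t-test crude and plans an adjusted coefficient; the fault is that neither is designated. The crude rejection rates above therefore describe an analysis that the article does not say it will rely on. Nor is the crude test underpowered on its own terms: it has its planned 80% for 0.67 if the SD is 1 and the groups are balanced.

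A reader might also infer that baseline GCII will usually be left out. That holds only for the screen on both. Under an outcome-only screen, a correlation of 0.5 or more makes entry almost certain.

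Simulated false-positive rates of 11% to 13% for the screened model can be produced, but they need five confounders all pushing the same way plus the screen on both. An outcome-only screen gives about 7% to 8% in the same setting, and the article gives no basis for that many aligned confounders.

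Mitigating features are real. Norms partly handle age and education. Eligibility restricts age, EuroScore II, dementia and severe comorbidity. The stated aim is change from baseline, which, if analysed as such, uses the baseline in part. Finally, this is a condensed article, and a covariate list could sit in an analysis plan that is not shown.

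That last point does not dispose of the concern. The article does not leave selection to a later document; it fixes a selection rule, and that rule is ambiguous and guarantees nothing.

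**Conclusion.** The point stands in a conditional form. The article does not designate a primary analysis, selects confounders by a Pearson screen whose target is not stated, and does not guarantee that baseline GCII is in the model.

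If association with both treatment and outcome is required, which is a natural reading of confounding criteria, a 0.3 SD imbalance leaves 0.08 to 0.13 SD of bias, or 11% to 19% of the 0.67 target. The cost there is mainly bias and lost power; the false-positive rate is only slightly raised (5.4% to 5.9%). If the screen is outcome-only, bias from baseline GCII is near zero. All of this rests on assumed correlations, imbalances and a p < 0.05 threshold.

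The comparability conclusion in the Discussion does not follow from its premise under either reading.

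**What to change.** - Name as primary one linear regression of follow-up GCII on group, baseline GCII and a short fixed list already collected (for example EuroScore II, atrial fibrillation, and prior stroke or TIA), all kept whatever their p-values. With baseline GCII in the model, the group coefficient is the same whether the outcome is follow-up or change, so this also settles that ambiguity.
- For this model, drop the Pearson screen, the 10% rule and the significance-based choice of interactions.
- Report the t-test as descriptive.
- Replace the comparability claim with a table of baseline standardised differences. A propensity-weighted sensitivity analysis is optional.

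The cost is wording in the protocol and analysis plan, with no new data, and a few degrees of freedom out of about 72 evaluable patients (2 × 36). Unmeasured confounding remains and should be stated as a limitation.

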Neuropsychological Tests:The same clinical neuropsychologist will conduct the NPS evaluation at the three evaluation times, and the neuropsychologist will be blind to the patient’s treatment group.The neuropsychological battery will last approximately one and a half hours, and it will consist of tests sensitive to vascular cognitive impairment (VCI). Neuropsychological tasks will be categorized into four cognitive domains:
Attention and Psychomotor speed will be measured by the Digit Span forward subtest of the Wechsler Adult Intelligence Scale (WAIS-III) [38], the Symbol Digit Modality Test (SDMT) [39], the Symbol Search subtest of the WAIS-III [38], the Grooved Pegboard dominant hand [40] and the Trail Making Test part-A (TMTA) [39, 41].Verbal and visual memory will be evaluated with the Rey Auditory Verbal Learning Test (RAVLT) 15-word verbal learning test (RAVLT) [42] and the delayed memory recall of Rey's Complex Figure (RCF) [43].Executive functions will be measured by the Digit Span backward subtest WAIS-III [38], the Trail Making Test part-B (TMTB) [39, 41], and the Phonemic Verbal Fluency test (letter M) [44].Visuoconstructive and Visuospatial functions included the copy of Rey’s Complex Figure (RCF) [43] and Block design subtest of the WAIS-III [38].

Also general cognitive functioning will be evaluated before the neuropsychological battery using the MMSE and MoCA tests [31, 45].

The order in the administration of tests will be constant to avoid variability between subjects due to fatigue.

To control for type I errors associated with multiple comparisons and to summarize scores obtained from the wide range of tests used, we will compute a Global Cognitive impairment Index (GCII) as the primary outcome. To this end, all measures will be first transformed to standardized z scores using age and education level corrected norms. The GCII will be computed by averaging all z scores from the different measures and also separately for each cognitive dimension. The final GCII will be a z score with a mean of 0 and an SD of 1 with lower or negative scores reflecting a poorer performance.

In addition, all patients will be classified into one of three groups according to their performance on the neuropsychological battery: a group with no cognitive impairment, a group with mild cognitive impairment (MCI) and a group with moderate cognitive impairment.

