MCI will be defined when the results of one or more cognitive domains are 1.5 SD below the mean. Moderate cognitive impairment will be considered when the results of one or more cognitive domains are 2 SD below the mean [46].

5Advanced Neuroimaging study protocol:

Data acquisition

Assessments will be carried out at the CMCiB with an MRI (Cannon MRT-3020 Vantage Galan 3T) dedicated to biomedical research. We will use a 32-channel phased-array head coil with foam padding and headphones to restrict head motion and suppress scanner noise. The MRI protocol will include a set of magnetization-prepared rapid gradient echo (MP-RAGE) T1-weighted images (repetition time [TR]: 8.4 ms; echo time [TE]: 2.7 ms; field of view: 256 mm; flip angle: 9º; and voxel size: 1×1×1 mm3). T2*- weighted images will be acquired using a multi-echo sequence with the following acquisition parameters: repetition time [TR]: 845.8 ms; with the following echo times [TE]: 6.800, 13.600, 20.400, and 27.200 ms; field of view: 245 mm; flip angle: 20º, and voxel size: 0.80×0.80×3 mm3. Fluid Attenuated Inversion Recovery (FLAIR) image will acquire with the following acquisition parameters: repetition time [TR]: 7000 ms; echo time [TE]: 445.5 ms; inversion time [TI]: 2200 ms; field of view: 256 mm; flip angle: 90º; and voxel size: 1×1×1 mm3. DWI will acquire in 48 non-collinear diffusion directions, with a b-value of 1.000 s/mm2, with the following echo planar acquisition protocol: [TR]: 12447 ms; [TE]: 81 ms; field of view: 240×256 mm; flip angle: 90º; and voxel size: 2×2×2 mm3; phase-encoding direction: PA. Two images with a value of 0 s/mm2 and opposite phase-encoding directions (AP and PA) will also be acquired. Intravoxel Incoherent Motion images (IVIM-DWI) will also be acquired with a single-shot spin-echo echo-planar imaging sequence using the following acquisition protocol: [TR]: 6680 ms; [TE]: 90 ms; field of view: 240 mm; flip angle: 90º; and voxel size: 1.5×1.5×5 mm3 with six b-values (50 sec/mm^2^, 100 sec/mm^2^, 300 sec/mm^2^, 600 sec/mm^2^, 1200 sec/mm^2^, and 2400 sec/mm^2^ with three orthogonal acquisition directions for each b-value. Resting-state blood oxygen level-dependent data will be acquired using an echo-planar imaging sequence (repetition time = 2.25 s; echo time = 25 ms; flip angle = 90°; in-plane spatial resolution = 3 × 3 mm2; field of view = 240 × 240 mm2; slice thickness = 3 mm; number of slices = 37; number of volumes = 256; acquisition time = 8:32 min). Participants will be instructed to lie still with their eyes closed but remain awake.

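### The search for predictors of cognitive dysfunction is planned only as logistic regression on categorised z scores; a continuous model should lead and the logistic model support it

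*Protocol article*

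**What the plan says.** In the protocol article, the neuropsychological assessment part of the baseline procedures defines the primary outcome as an average of z scores, overall and by domain: "The GCII will be computed by averaging all z scores from the different measures and also separately for each cognitive dimension". There are four domains: "Neuropsychological tasks will be categorized into four cognitive domains".

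The same part also sorts patients into no, mild or moderate impairment. The cuts are taken on the domain scores: "MCI will be defined when the results of one or more cognitive domains are 1.5 SD below the mean", and "Moderate cognitive impairment will be considered when the results of one or more cognitive domains are 2 SD below the mean".

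Statistical considerations sizes the study for a 0.67 z-score difference with SD 1, two-sided, giving 36 per group, or 40 after 10% loss. The treatment comparison is a t-test followed by a linear regression adjusted for confounders. For predictors the method changes: "The search for independent predictors of neuropsychological dysfunction will be carried out using a predictive approach of hierarchical logistic regression", with backward stepwise selection. No reason is given for the change, and no continuous predictor model is planned beside it.

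**The concern.** To fit a logistic model, the continuous scores must first be reduced to classes. With a cut at -1.5 SD, a patient at -1.4 counts the same as one at +1, and a patient at -1.6 the same as one at -4. With about 72 evaluable patients that lost information matters. A real predictor can fail to reach significance and be read as having no independent association, and the odds ratios depend on where the cut falls.

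This is separate from backward selection and from the number of events per candidate variable. The loss arises with a single pre-specified predictor and no selection step, so changing the selection method alone would not recover it.

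**Working it through.** **Inputs from Statistical considerations:** difference 0.67, SD 1, 36 per group, two-sided 5%. **Assumed, because the documents do not give them:** the predictor is binary and balanced (36 v 36); it is worth the same 0.67 SD; scores are normal and every exposed patient shifts equally; the prevalence of dysfunction; the correlation between domains.

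**1. The plan's own figure.** Noncentral t: noncentrality = 0.67 × √(36/2) = 2.84, df = 70, critical value 1.994. Power is 80.05% at 36 per group and 78.9% at 35. 36/0.90 = 40. Both stated figures reproduce.

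**2. One index cut at c.** Impaired proportions are p1 = Φ(c) and p2 = Φ(c + 0.67). Power of the logistic likelihood-ratio test is found by summing the two binomial distributions (n = 36 each) over all tables with a statistic above 3.84.

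| Cut c | p1 v p2 | Overall | Power | Loss from 80% |
|---|---|---|---|---|
| -1.5 | 6.7% v 20.3% | 13.5% | 42% | 38 points |
| -1.43 | 7.6% v 22.4% | 15% | 44% | 36 |
| -1.05 | 14.7% v 35.3% | 25% | 55% | 25 |
| -0.60 | 27.3% v 52.7% | 40% | 60% | 20 |
| -0.335 | 36.9% v 63.1% | 50% | 60% | 20 |

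**3. The protocol's rule, at least one of four domains below -1.5 SD.** Simulated with four domain scores of SD 1 and common correlation ρ. Each domain is shifted by 0.67 × √(ρ + (1 - ρ)/4), so that their mean, standing in for the GCII, shifts by 0.67 of its own SD.

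| ρ | Overall impaired | Continuous test | Logistic likelihood-ratio test | Three ordered classes |
|---|---|---|---|---|
| 0.3 | 31% | 80% | 46% | 45% |
| 0.5 | 29% | 80% | 50% | 49% |
| 0.7 | 25% | 80% | 51 to 52% | 51% |

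A plain chi-square comparison of the two proportions gives 44 to 50%. The overall reading is about 45 to 52%, and using all three ordered classes does not recover the loss.

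**4. Continuous predictor of equal strength.** r = 0.67/√(0.67² + 4) = 0.32, n = 72. Simulated power is 78 to 80% for linear regression. For logistic regression it is about 42 to 43% at 15% prevalence, 51 to 53% at 25% and 57 to 59% at 40%.

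**5. Predictor that harms only a subset (illustrative).**

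| Exposed patients affected | t-test | Logistic, cut -1.5 | Logistic, cut -1.0 |
|---|---|---|---|
| 25% fall by 2 SD | 43% | 50% | 42% |
| 30% fall by 2.5 SD | 68 to 69% | 77% | 63% |

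Here the cut does as well or better at -1.5 SD and about as well or somewhat worse at -1.0 SD.

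**The case against.** Five points can be made for the plan.

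- **Different question.** The logistic model asks who meets an impairment definition, and linear regression asks what moves the mean score. The Background lists as a weakness of earlier studies that decline was often just a fall in mean test scores, which is a motive for a categorical outcome. This stands, and is why the logistic model should be kept.
- **The procedure effect is covered.** A reader might infer that a true SAVR versus TAVI difference would be missed. The documents do not support that: the comparison is made by t-test and adjusted linear regression. Covariates that pass the confounder screen also enter that linear model, though as adjustment terms and not as a predictor analysis.
- **Ancillary analysis.** None of the four specific objectives in the Background is a predictor search, and the primary outcome and sample size stay continuous. This stands and limits the weight of the point.
- **Outcome not defined for this model.** The section does not say how dysfunction is coded in the logistic model. A condensed article may leave that to the full plan, so it is no fault in itself. However, any logistic coding of the battery scores requires categories.
- **The size depends on assumptions.** The 42% figure comes from cutting a single index at -1.5 SD, whereas the protocol applies that cut to domains. The 25% and 40% prevalences match decline rates that the Discussion reports from a cited study, not this trial's impairment classes. If decline is confined to a subset, which is plausible with embolic injury, the direction can reverse. This stands.

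**Conclusion.** The concern holds as a modest improvement to a secondary analysis. The plan measures cognition on a continuous scale and already uses linear regression for the treatment comparison, yet searches for predictors only on a categorised version.

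Under a uniform 0.67 SD shift with normal scores, power falls from 80% to about 45 to 52% under the protocol's domain rule, with inter-domain correlation assumed at 0.3 to 0.7. For a cut of a single index it falls to about 42 to 60%, at an assumed prevalence of 13 to 50%.

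A reader might infer a general loss of 20 to 38 points whatever the predictor. The documents do not support that: they give no prevalence, they set no -1.5 SD cut of the GCII (the source of the 38), and the loss is smaller or absent when only some patients are harmed. Nor is the primary GCII comparison weakened.

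**What to change.** In Statistical considerations, make multivariable linear regression of follow-up GCII, with baseline GCII as a covariate, the main analysis of predictors, with the domain z scores as secondary outcomes. Keep the logistic model on the impairment classes already defined in the neuropsychological assessment, labelled as supportive. It then still answers who meets the definition and still covers decline confined to a subset.

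The cost is a sentence or two of wording and one additional model. The battery is given at baseline, one month and one year, so no new data are needed. The small downside is that the main coefficients are in z-score units rather than odds ratios, which clinicians may find less familiar; the supportive model supplies the odds ratios.
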